## Abstract

**Background:**

In out-of-hours urgent care practices in Germany, physicians of different specialties care for a large number of patients, most of all unknown to them, resulting in a high workload and challenging diagnostic decision-making. As there is no common patient file, physicians have no information about patients’ previous conditions or received treatments. In this setting, a digital tool for medical history taking could improve the quality of medical care. This study aims to implement and evaluate a software application (app) that takes a structured symptom-oriented medical history from patients in urgent care settings.

**Methods:**

We conduct a time-cluster-randomized trial in two out-of-hours urgent care practices in Germany for 12 consecutive months. Each week during the study defines a cluster. We will compare participants with (intervention group) and without app use (control group) prior to consultation and provision of the self-reported information for the physician. We expect the app to improve diagnostic accuracy (primary outcome), reduce physicians’ perceived diagnostic uncertainty, and increase patients’ satisfaction and the satisfaction with communication of both physician and patient (secondary outcomes).

**Discussion:**

While similar tools have only been subject to small-scale pilot studies surveying feasibility and usability, the present study uses a rigorous study design to measure outcomes that are directly associated with the quality of delivered care.

**Trial registration:**

The study was registered at the German Clinical Trials Register (No. DRKS00026659 registered Nov 03 2021. World Health Organization Trial Registration Data Set, https://trialsearch.who.int/Trial2.aspx? TrialID = DRKS00026659.

## Background

In Germany, ambulatory out-of-hours care is provided through walk-in practices run by the Associations of Statutory Health Insurance Physicians (in German: ‘Kassenärztliche Vereinigungen’, KV). Compared to general or family medicine practices, these urgent care clinics have limited diagnostic and therapeutic possibilities and are frequented by a heterogeneous group of patients of various ages and health complaints. Physicians almost exclusively provide care to patients they do not know from previous encounters. The physicians in these out-of-hour practices have various specialist backgrounds (i.e. not only specialized in general practice but, for example, in otolaryngology, gynecology, or dermatology) and professional experience. With time constraints and a high need for diagnostic and therapeutic clarification, the provision of care in out-of-hours consultations is considered highly complex and stressful [1]. Misdiagnosis, especially non-recognition of severe conditions that lead to (preventable) dangerous courses and subsequent delayed or inappropriate treatment, may occur as well as overuse of medical resources through unnecessary diagnostic and therapeutic measures or unnecessary referrals to emergency rooms or hospital admissions. Both are inefficient and increase costs for the health care system [2, 3].

Research findings suggest that only 70–85% of the diagnoses made by physicians of different specialties are accurate [4]. Errors related to delayed or missed diagnoses are most likely to harm patients or precipitate admission to hospital [5]. Some of these errors could be avoided if physicians had access to patients’ medical history so that they could include this information in their clinical assessment and decision-making [3, 6]. However, time for taking medical history is tight: A consultation in general practice in Germany takes 7.6 min on average [7]. During this time span, a physician obtains the patient’s medical history, responds to the patient’s concerns, performs a physical examination, considers different diagnoses, performs shared decision making, explains management, prescribe drugs and documents the visit in a note.

Collecting information on a patient’s medical history during the waiting time could help make better use of the limited consultation time and increase patients’ safety [8]. Studies have shown that questionnaires completed before the medical consultation enhance the safety of treatment and make it easier to assess individual risk constellation [9, 10]. The information provided by patients has been found to be more accurate and correct than those previously assessed by the physician [11]. In addition, a meta-analysis of randomized-controlled studies showed that patients were significantly more satisfied if they were asked about their expectations of the upcoming visit [12]. As this information is available to physicians and practice staff prior seeing the patient, it can be used for preparation, scheduling or even triage and may reduce documentation work. It can be assumed to be especially helpful in settings where a physician is providing care to a previously unknown patient.

Digital tools to obtain patients’ medical histories have been designed and evaluated for some specialties such as cardiology [13] or gastroenterology [14, 15] but only few are available for general practice [16, 17]. In a recently published scoping review on 18 digital tools designed for obtaining medical history from patients or caregivers [18], eight of the tools were not tailored to a specific patient subpopulation. While the research on these tools mainly comprise proof-of-concept and general usability, studies on patient experience and its impact on health outcomes are sparse.

### Study objectives

In the project “DASI” (acronym for ‘Digital assistierte Informationserfassung vor der Sprechstunde’; i.e. ‘Digitally supported system to obtain patient’s medical history before consultation’), we aim at piloting and evaluating a software application (app) developed for a structured symptom-oriented medical history taking among patients with acute medical complaints in general practice. While accuracy of obtained information and usability has been studied in another project [19], this study firstly addresses whether an app designed to obtain medical history before consultations in addition to regular medical history taking can improve diagnostic accuracy. Secondary, we aim to evaluate whether the use of the app prior to medical consultation increases patient satisfaction and reduces physicians’ perceived diagnostic uncertainty.

Within the framework of explorative data analysis (machine learning and data mining), complex prediction models are modeled based on the medical history data. The data is used to illustrate the potential use and opportunities of the software application for intelligent patient management, diagnostic and scientific purposes.

## Methods

### Software

We use an app that is designed to take the history of present illness from patients in general practice. The app covers the most common complaints in general practice. General practice touches on almost all medical specialties which entails that a respective tool must cover this broad and comprehensive field. A previous version of the app was originally developed for non-German-speaking patients by medical experts by aidminutes GmbH (Hamburg/Buchholz in der Nordheide, Germany) and piloted in a reception facility for refugees and asylum seekers [16, 20]. For this study, content and query structure were revised and further refined to meet requirements in out-of-hours practices. These adaptions were carried out jointly by aidminutes GmbH and experienced researchers from the Department of General Practice at the University Medical Center Göttingen. While the app is also available in other languages, the German language user interface is exclusively used for this study.

Patients choose their acute complaint(s) and are then guided through a query with questions related to their complaints, for example about specific symptoms, relevant pre-existing conditions, previous treatments, or medication. Depending on patients’ answers, follow-up questions regarding the current symptoms may be triggered. Questions and answers are phrased in plain language, the design is kept simple and navigation is intuitive, so that the app can be used by patients without prior instruction.

After completing the app, a structured summary of the medical history is compiled which can be transferred to the patient’s electronic medical record (EMR). The physicians can review this information before the patient encounter and can prepare themselves for the consultation and patients’ health needs.

For this study, participants used the app on iPad minis (6th generation, Apple, Inc, Cupertino, CA, USA).

### Study design

To evaluate the effect of the developed app, a two-center, open-label, cluster-randomized trial (CRT) time-periods as clusters and groups under intervention or control condition will be conducted. In the intervention group, patients use the developed app in the waiting area before the encounter and the obtained information is available for the medical assistants and physicians before the consultation. In the control group, patients use the app after the consultation. The entered information is thus not available before the encounter. Clusters are defined as time periods of one week. In each week one practice is in the intervention group, the other one in the control group. The randomization of control and intervention group takes place before the start of the study in blocks of two weeks (see Fig. 1). Due to the two-weeks-block randomization, it is possible that a practice is in the control or intervention group for a maximum of two consecutive weeks.

**Fig. 1 Fig1:**
[figure not shown]
Example of two-week block randomization of participating out-of-hours practices for the first 6 weeks

The advantage of cluster randomization compared to patient-level randomization is that the data collection procedure remains the same during the service time. This prevents, for example, a physician from adapting their medical history taking of control group patients to those of intervention group patients, i.e. the cluster randomization minimizes the risk of contamination.

Data collection will take place for 12 consecutive months to control for seasonal effects. We will thus have aggregated data for two six-month periods for each intervention and control group from both centers.

#### Primary outcome

Diagnostic accuracy is the primary outcome of this study. For this purpose, the diagnoses of the attending physicians are compared with the diagnoses given by an expert committee consisting of three physicians experienced in general practice or family medicine. For each encounter, this expert committee will review the information obtained from the patient using the app (self-reported medical history), the documentation of the attending physician and the information provided by the patient about further treatment through a follow-up-survey, 14 to 21 days after the initial consultation. The committee is blinded whether a patient was assigned to intervention or control group. The decision of the committee is reached in a staged process: First, two physicians of the committee are asked to provide diagnose(s) for the encounter independently using the ICD-10-GM codes (10th revision of the International Statistical Classification of Diseases and Related Health Problems, German Modification) version 2019 by the World Health Organization (WHO; WHO Version 2019). If these diagnoses match, they will be compared to the diagnoses made by the physician of the out-of-hours practice. If the diagnoses of the expert committee physicians differ, a consensus on a diagnosis is reached with a third physician, which is then compared with the diagnosis made in the out-of-hours practice.

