#### Intervention group

In the intervention group, the participant then receives a tablet with the app installed. The participant completes the digital medical history in the waiting area. At the end of the survey, the app generates a report from the participants’ responses, which is subsequently transferred to the EMR via a scanned QR-code. This report is available to the physician before the consultation. No data remains stored on the device itself.

When they are next in line, the participant goes to the doctor’s office for consultation. After the consultation, both the participant and the physician are asked to fill out a short questionnaire. The participant will be asked questions about their satisfaction with the consultation (EUROPEP) and about communication (PSQ) and socio-demographic questions. These questions will be presented on the study tablets using the survey software Limesurvey. Subsequently, each participating patient receives a compensation of EUR 15.

The physician is asked to document the ICD-10-GM code (WHO Version 2019) of the (preliminary) diagnosis, to answer questions about their experience of uncertainty regarding this diagnosis and questions matching those that the participant is asked about communication. Additionally, we will collect data regarding the physicians’ specializations and experience (i.e. year of approbation and year of the first specialist examination).

After 14 to 21 days, we conduct a short follow-up to ask participants about their further treatment (e.g. by their family doctor, specialist treatment and hospital admissions). Participants may answer these questions via an online questionnaire (accessed using a personalized link which is sent per e-mail or text message) or by telephone (interview conducted by a study nurse).

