#### Control group

After approving consent and data protection declaration, participants of the control group transition to their medical consultation and will use the app for medical history after the encounter. Information gathered from the app is not transferred to the EMR. Therefore, contrary to interventional group, for control participants, physicians do not have additional information collected by the app. After the consultation, the participant and the physician are asked to complete questionnaires as described for the intervention group. Remuneration and follow-up procedure are then identical to the intervention group.

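### The expert committee is said to be blinded, but it reads the attending physician's documentation, and nothing in the article keeps arm-revealing text or the diagnosis under test out of that material

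*Protocol article*

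**What the plan says.** Under Primary outcome, the Protocol article lists three sources for the reference diagnosis. Two are named thus: "this expert committee will review the information obtained from the patient using the app (self-reported medical history), the documentation of the attending physician". The third is what patients report about later care in a survey two to three weeks after the visit. The same section says that "The committee is blinded whether a patient was assigned to intervention or control group". The procedure is staged: "First, two physicians of the committee are asked to provide diagnose(s) for the encounter independently using the ICD-10-GM codes". A third physician joins if the two differ, and the result is then compared with the practice's diagnosis.

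The electronic record differs by arm. Under Intervention group, the app produces a report "which is subsequently transferred to the EMR via a scanned QR-code", before the consultation. Under Control group, "Information gathered from the app is not transferred to the EMR". Control patients complete the app after the consultation, so an app history exists for both arms.

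On the diagnosis under test, the Intervention group section says "The physician is asked to document the ICD-10-GM code (WHO Version 2019) of the (preliminary) diagnosis", along with the questions on uncertainty and communication. The Control group section refers back to the same questionnaires.

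Study design describes the trial as open-label, with each practice wholly in one arm for a given week.

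**The concern.** Two separate protections of the primary outcome are involved.

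- **Blinding.** An app report stored in the record, or a remark in the notes that refers to it, can occur before the consultation in the intervention arm only. A reviewer who meets either learns the arm. Because a practice-week has a single arm, one such record can reveal the arm of every participant from that practice and week if practice and date are visible.
- **Independence.** The physician being scored wrote part of the evidence that decides whether that physician was right. If the notes include the diagnosis, reviewers may adopt it, and a wrong diagnosis then counts as correct.

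The trial is open-label and the outcome is a judgement, so committee masking is its main safeguard. This is also the only endpoint that Statistical design does not call exploratory. Once the committee has read unmasked material, no analysis can undo it.

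**Working it through.** **Step 1: the passages side by side**

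| Question | What the article says |
|---|---|
| Is the committee blinded to arm? | Stated under Primary outcome; no method given |
| Does it read the physician's documentation? | Yes, a named input |
| Is the content of that documentation defined? | No |
| Is the app report in the electronic record? | Intervention yes, control no |
| Does the committee receive the app history? | Yes, for each encounter in both arms |
| Is the attending diagnosis withheld until the committee decides? | Not stated; the comparison comes afterwards |
| What does the independence of the raters cover? | The two raters relative to each other, not relative to the attending physician |

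**Step 2: the plan's own figures** (Sample size estimation)

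Inputs: accuracies 75% and 85%, two-sided 5%, power 90%, ICC 0.01, 36 patients per two-week cluster, dropout 5%. One-week clusters of 18 follow by halving.

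- Per group: [1.960·√(2·0.80·0.20) + 1.282·√(0.75·0.25 + 0.85·0.15)]² / 0.10² = 334.2, rounded up to 335 (stated 335). Power at 335 is 90.1% (stated 90%).
- Two-week clusters: design effect 1 + 35·0.01 = 1.35; 670·1.35/0.95 = 952.1 (stated 952).
- One-week clusters: design effect 1 + 17·0.01 = 1.17; 670·1.17/0.95 = 825.2 (stated 825).

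All reproduce. The concern is with how the endpoint is ascertained, not with the sample size.

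**Step 3: equal anchoring in both arms** (q is an assumption)

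Let the committee adopt a share q of the physician's wrong diagnoses. Observed accuracy is then p + q(1 − p). Power uses the same two-proportion formula with 335 effective patients per arm.

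| q | Control | Intervention | Difference (points) | Odds ratio | Power |
|---|---|---|---|---|---|
| 0% | 75.0% | 85.0% | 10 | 1.89 | 90% |
| 10% | 77.5% | 86.5% | 9 | 1.86 | 86% |
| 20% | 80.0% | 88.0% | 8 | 1.83 | 81% |
| 30% | 82.5% | 89.5% | 7 | 1.81 | 74% |
| 40% | 85.0% | 91.0% | 6 | 1.78 | 67% |

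The section Big Data objectives expects about 1,000 patients. Over 52 weeks that is 1,000/52 = 19.2 per cluster, a design effect of 1 + 18.2·0.01 = 1.18, and 950/1.182/2 ≈ 402 effective patients per arm. Power is then 94% at q = 0, 87% at q = 20% and 75% at q = 40%.

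**Step 4: anchoring that differs by arm** (also assumed, 335 effective per arm)

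- No true effect (75% in both arms), anchoring in the intervention arm only. At q = 10% accuracy reads 77.5% versus 75%, a spurious 2.5 points, with an 11.5% chance of a significant result in favour of the app. At q = 20% it reads 80% versus 75%, 5 points and 34%. The nominal chance in that direction is 2.5%.
- True effect 75% versus 85%, anchoring in the control arm only. At q = 20% control reads 0.75 + 0.20·0.25 = 80%, so the difference halves to 5 points. At q = 40% control reads 85% and the difference vanishes.

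**The case against.** A reader might infer that the claimed blinding cannot hold. The documents do not support that. The article affirms blinding, masked extracts are compatible with its text, and a condensed article may leave their preparation to a fuller document. It puts the app report in the electronic record but does not say that the committee reads that record, and it lists the app history and the physician's documentation as separate sources. Because the committee receives an app history in both arms, its mere presence reveals nothing.

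A reader might also infer that the reviewers see the very diagnosis they are judging. That is plausible but not stated. The code is requested with the post-consultation questionnaire, and the comparison is placed after the committee's decision. What remains is that this order fixes when agreement is scored, not what the raters have read by then.

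Use of the attending record is not a flaw in itself, since examination findings may be available nowhere else. This stands, and the notes should not be dropped.

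On size, every q is assumed, and nothing in the documents indicates anchoring in one arm only. The model reports an odds ratio, which under equal anchoring moves only from 1.89 to 1.78. That is true of the estimate, but power still falls, because rates nearer 100% carry less information per patient. On the log-odds scale at 335 per arm, the effect divided by its standard error goes from 0.636/0.198 = 3.21 to 0.579/0.245 = 2.37, which gives power of about 89% and 66%.

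**Conclusion.** The point holds as a risk that the stated procedure leaves open, not as a demonstrated breach. The physician's own documentation is a prescribed input to the standard against which that physician is scored. The electronic record differs by arm. Nothing in the article keeps the app report, references to it, or the attending diagnosis from the reviewers. Blinding is asserted but exposed, and independence from the diagnosis under test is not secured.

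Equal anchoring would mainly cost power: a fall from 90% to between 86% and 67% for assumed rates of 10% to 40%, smaller if about 1,000 patients are enrolled, with little change in the odds ratio. Unequal anchoring is the more serious possibility because it can bias the result either way. Its likelihood cannot be judged from the documents. The matter should be settled before committee review starts.

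**What to change.** State and apply a masking step under Primary outcome:

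1. Before review, existing study staff redact from the physician's documentation the diagnosis text and ICD code, the imported app report and any reference to it. The examination findings stay.
2. The app history reaches the committee in one identical layout, without time stamps, in both arms.
3. Practice and date are hidden where feasible.
4. The attending diagnosis is disclosed only after the committee's diagnosis is locked.

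The cost is a small amount of handling per case and a few sentences in the plan. No extra patients or assessors are needed, and the sample size is unchanged. If such masking is already in place, a sentence saying so closes most of the point. Redaction cannot remove all dependence, because the findings and reasoning that a physician records are shaped by the diagnosis in mind. That remainder should be stated as a limitation.

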#### Secondary outcomes

Secondly, we hypothesize that the app reduces physicians’ perceived diagnostic uncertainty, increases patients’ satisfaction and the satisfaction with communication of both. Secondary outcomes of the clinical trial are therefore:

the patients’ overall satisfaction,the patients’ satisfaction with the communication with the physician,the physicians’ satisfaction with the communication with the patient, and.the physicians’ perceived diagnostic uncertainty.

This data will be obtained using questionnaires for both participants and physicians. Participants’ overall satisfaction with the consultation will be assessed using questions from the standardized and validated questionnaire European Project on Patient Evaluation of General Practice Care Questionnaire (EUROPEP) in German language. This instrument comprises short questions on the quality of primary care which participants rate on a five-point Likert scale ranging from “poor” to “excellent” [21, 22]. The questions focusing on the communication for both, participants and physicians, are based on the Patient Satisfaction Questionnaire (PSQ) [23–25]. Each item is a secondary endpoint that will be analyzed individually.

